### Data analysis

A conventional content analysis method, introduced by Graneheim & Lundman (2004), is used for data analysis [15]. Each interview will be transcribed immediately at the end of recording. After extracting the general idea, the narrative will be analyzed line by line, and its meaning units will be identified. Compact meaning units and codes will be extracted from these meaning units. After extracting the primary code, the data will be reduced and divided into sub- categories and main categories, based on their appearance.

### Rigor and trustworthiness

For reliability and validity analysis, four criteria are suggested: credibility, dependability, transferability, and confirmability [16]. Different measures will be taken into consideration in order to improve credibility of this study, such as selecting the participants with maximum variety, spending sufficient amount of time on data collection, performing in-depth interviews in different locations and times, and mixing multiple data collection methods including individual interviews, focused group discussions, and field noting. For verification of extracted codes and data or their modification, they will be reviewed by the participants.

For confirming the reliability of the findings, some examples of code extraction methods and their corresponding interview narratives will be reviewed by an external supervisor in order to control the accuracy of researcher’s perception and to find contradictory cases. For increasing transferability, study findings will be presented to people who have similar characteristics with the participants in order to compare the results of this study with their own experiences. Regarding verification, the researcher will explain the whole procedure, including recording, transcription, code extraction, and categorization. In order to verify the coding procedure, some of the research colleagues and faculty members, who are acquainted with qualitative research analysis and do not want to participate in this research, are asked to review the procedure.

### Second phase: Designing the intervention program

After collecting the required data by qualitative study, the second phase of the study starts. The purpose of this phase is designing an intervention program for improving eating behavior in adolescent girls with PCOS. In this phase, the required strategies are extracted based on the results of qualitative phase and a literature review of papers and texts. These strategies will be validated by expert panel. The method of review will be narrative review with searching in electronic and library resources including reference books and theses. Multiple databases are available for searching the related papers, such as Scopus, MEDLINE, Ovid, ProQuest, Cochrane Library, Science Direct, Web of Science, PubMed, Embase, Magiran, SID, Google Scholar and CINAHL.

In this phase, all the English and Persian qualitative, quantitative, and mixed methods studies on eating behaviors, eating problems and healthy eating behavior facilitators in adolescent girls with PCOS, which have been published during 1991 to 2018, will be studied and analyzed. In the next phases, search will be narrowed down to specific mixed keywords, including “healthy eating behaviors”, eating behaviors in adolescent girls with PCOS and “eating problems”, eating behaviors in adolescent girls with PCOS and “nutritional health needs”, eating behaviors in adolescent girls with PCOS and “nutritional health promotion”, eating behaviors in adolescent girls with PCOS and “weight management”, eating behaviors in adolescent girls with PCOS and “lifestyle and behavioral management”, eating behaviors in adolescent girls with PCOS and “elimination of eating problems”, eating behaviors in adolescent girls with PCOS and “nutritional management”, eating behaviors in adolescent girls with PCOS and “life style modification”, eating behaviors in adolescent girls with PCOS and “nutritional intervention”.

### Holding a panel of experts

The objectives of this phase is to extract relevant eating strategies for having healthy eating behaviors in adolescent girls with PCOS from qualitative study and analyze the interview narratives in expert panel in order to prioritize their function. Then, the suitable interventional program will be selected and executed in the quantitative phase based on this prioritization. For this end, a decision making matrix will be extracted for prioritization of the extracted strategies from qualitative study and literature review of papers and texts. In this matrix, each strategy is provided with a score from one to three based on three criteria of costs, ease of execution, and time. This matrix will be sent for some specialists in the Delphi Round 1, average score will be calculated for each solution, high priority strategies will be identified, and consequently, a suitable intervention method will be selected. In Delphi Round 2, the selected intervention method will be evaluated qualitatively in a meeting with the presence of research team and panel members (nutrition and food sciences specialists, psychologists, gynecologists, reproductive health professionals, endocrinologist and authorities of the adolescents and youth health). A copy of the intervention strategy will be presented to the experts who will be returned to the researcher at the end of the meeting. Comments and suggestions will be collected and applied in order to finalize and execute the strategy in the third phase (quantitative study).

### Third phase: Quantitative study

#### Type of quantitative study

Quantitative phase of the study will be carried out using a two-group clinical trial.

#### Research population

The targeted population for quantitative study is all adolescent girls with PCOS referred to gynecology training clinics covered by Shiraz University of Medical Sciences.

#### Research sample

Study sample includes adolescent girls with PCOS who will be selected by convenience sampling and have all the inclusion criteria.

#### Research environment

This study will be carried out in four gynecology training clinics covered by Shiraz University of Medical Sciences. The reason for selecting such kind of environment is easy access to adolescent girls with PCOS and characteristics of the research unit.

#### Sample size

Sample size will be 36 participants in each group considering 95% confidence interval, 80% trial power, S = 0.1–0.25 and 10% loss.

#### Sampling method

This clinical trial has one intervention group and one control group. After identifying the clinics covered by Shiraz University of Medical Sciences, four gynecology training clinics will be selected non-randomly. Afterwards, 18 adolescent girls with PCOS with inclusion criteria will be selected from each center via convenience sampling method.

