#### The implementation method

The researcher will implement the designed program after obtaining the necessary coordination with authorities of four gynecology training clinics covered by Shiraz University of Medical Sciences. This is done by referring to the gynecology training clinics and presenting a letter of introduction to the authorities of those centers regarding research objectives. After that, the researcher will be allowed to access to phone numbers of adolescent girls with PCOS and call her in order to explain research objectives and invite them to participate in the research. If they are willing to cooperate, and have all the inclusion criteria, they will be selected by convenience sampling method with their informed consent.

Adolescent girls^,^ knowledge, attitude, subjective norms, perceived behavioral control, behavioral intention and eating practice (behavior) will be considered as the suggested outcomes. Before intervention, the questionnaires will be filled by them in each of the two groups. Furthermore, the questionnaires will be refilled by adolescent girls with PCOS three months after the intervention.

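### The third phase describes no random allocation to intervention or control and does not say whether girls or clinics are assigned, so a group difference is open to selection and possibly to clinic effects

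*Protocol article*

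**What the plan says.** The protocol article describes the third phase in these steps.

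- Type of quantitative study: "Quantitative phase of the study will be carried out using a two-group clinical trial". The word randomised is not used.
- Sampling method (third phase): "This clinical trial has one intervention group and one control group". On sites and participants, "four gynecology training clinics will be selected non-randomly. Afterwards, 18 adolescent girls with PCOS with inclusion criteria will be selected from each center", the girls by convenience.
- Sample size: "Sample size will be 36 participants in each group", including 10% loss.
- The implementation method: the researcher who implements the programme obtains telephone numbers, calls and invites the girls. Those who are eligible and willing enter as follows: "they will be selected by convenience sampling method with their informed consent". The text then turns to the outcomes and to the baseline measurement: "Before intervention, the questionnaires will be filled by them in each of the two groups". The questionnaires are repeated three months after the intervention.
- Data analysis (third phase): two-group and paired tests are listed, with ANCOVA to adjust for intervening variables that are not named.

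The abstract and the Methods/design overview mention no randomisation either. In the text shown, the only form of the word random is in the statement on how clinics are chosen.

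**The concern.** The objective of the third phase is causal: to establish whether the programme improves eating behaviour, with a view to its becoming an education guideline. That needs groups that differ only by chance, apart from the programme. The article gives the choice of clinics, the number per clinic, the route of entry and the baseline measurement, but no step that assigns anyone to a group.

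Two routes to bias follow. First, if the person who telephones and enrols the girls also decides, or knows, who gets the programme, more motivated girls may end up in the intervention group. Attitude, norms, perceived control, intention and reported eating are all likely to depend on motivation. Second, if whole clinics are assigned, differences between clinics in clientele and routine counselling become part of the apparent programme effect. The only stated protection is ANCOVA, which corrects for what is measured and entered in the model.

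**Working it through.** **1. What the counts show.** The inputs are 4 clinics and 18 girls per clinic (Sampling method) and 36 per group (Sample size).

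- 4 × 18 = 72 and 2 × 36 = 72, so the counts agree.
- Two whole clinics per group: 2 × 18 = 36.
- Half of each clinic: 18 / 2 = 9, and 4 × 9 = 36.

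Both layouts give 36 per group, so the arithmetic cannot tell which is meant.

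**2. What the trial can detect.** The article gives no target difference, so the 36 cannot be reproduced forward. Working backwards, 36 × 0.9 = 32.4, or about 32 evaluable per group. With two-sided 5% (read from the 95% confidence level) and 80% power:

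- standard error in SD units = √(2/32) = 0.25
- detectable difference = 0.25 × (1.960 + 0.842) = 0.70 SD

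**3. Illustration of selection bias (assumed values).** Suppose that the programme has no effect and that the groups differ systematically by b SD in an unadjusted comparison. The chance of a significant result is P(Z > 1.96 − b/0.25) + P(Z < −1.96 − b/0.25).

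| b (SD) | b / 0.25 | Chance of a significant result |
|---|---|---|
| 0 | 0 | 5% |
| 0.1 | 0.4 | 6.9% |
| 0.2 | 0.8 | 12.6% |
| 0.3 | 1.2 | 22.4% |
| 0.5 | 2.0 | 51.6% |

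A bias of 0.3 SD is 0.3 / 0.70 = 43% of the detectable difference.

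**4. Illustration if whole clinics are assigned (assumed: two per group, 16.2 evaluable girls per clinic, true difference 0.70 SD).** Design effect = 1 + (16.2 − 1) × ICC, and effective number per group = 32.4 / design effect.

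| ICC (assumed) | Design effect | Effective n per group | Power, normal approximation | Power, t-test with 2 df |
|---|---|---|---|---|
| 0 | 1.00 | 32.4 | 80% | 36% |
| 0.01 | 1.15 | 28.1 | 75% | 32% |
| 0.05 | 1.76 | 18.4 | 57% | 24% |

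The 2 degrees of freedom are 4 clinics less 2 groups. Also, four clinics can be split two and two in only 4!/(2! × 2!) = 6 ways. An exact two-sided test over those splits therefore cannot give a p-value below 2/6 = 0.33.

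**The case against.** The strongest reply is that selection is not allocation. The statement that clinics are chosen non-randomly concerns sites, and convenience sampling concerns who is approached. Girls or clinics selected in this way can still be randomised, and most randomised trials recruit like this. This stands. A reader might infer that the article declares a non-randomised comparison, or that these sampling features alone rule out a causal reading. It does not: it is silent on assignment.

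Three further inferences are tempting and are not supported.

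- That two whole clinics form each group. The counts fit 9 and 9 within each clinic equally well.
- That the groups already exist before baseline. The sentence on the questionnaires says only that both groups give baseline data.
- That a baseline difference passes in full into the result. All six outcomes are measured at baseline and ANCOVA is planned, so adjustment for the baseline score would remove part of it. What remains is imbalance in things not measured or not in the model.

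The outcomes are also not equally exposed: knowledge is scored on correct answers.

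Finally, this is a condensed article. The study diagram and the full protocol are not shown, and either may state the allocation. That calls for caution in the wording but does not dispose of the point. How the groups of a controlled trial are formed is its central design fact. An article that gives selection, enrolment and baseline in this detail does not commonly leave it to another document.

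**Conclusion.** The point holds in this form: the article describes no random allocation and does not name the unit of assignment, while the third phase has a causal aim. A team following the text as written could obtain a convenience-sampled comparison protected only by ANCOVA on unnamed variables.

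If allocation is in fact non-random, the programme's effect cannot be separated from selection. If it is random, the protocol omits its main safeguard, and the reader cannot tell whether an analysis by girl or by clinic is needed.

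The documents put no size on the bias. The 0.3 SD, the ICC values and the layout of two clinics per group are assumptions, used only to show that moderate bias or clustering would matter in a trial with about 32 evaluable girls per group. No corrected sample size follows from this point.

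**What to change.** Under Sampling method and The implementation method of the third phase, state that:

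- each girl gives consent and completes the baseline questionnaires first;
- she is then randomised 1:1 within her clinic, 9 to intervention and 9 to control, from a computer-generated list in blocks that add up to 18 per clinic;
- the list is concealed from the researcher who recruits, for example in sealed numbered envelopes held by someone else.

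Under Data analysis, make the group comparison an ANCOVA adjusted for clinic and for the baseline score of the outcome.

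The cost is one amendment, a list and envelopes, with no extra girls, clinics or staff. The downside is that girls in the same clinic may share material. This would dilute the effect, and so cost some power, rather than create a false one. Separate session times would limit it.

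If clinics must be the unit, for instance to avoid such sharing, say so, randomise the clinics, account for clustering with four clinics, and limit the causal claim accordingly. If allocation is in fact not random, call the study a non-randomised comparison and restrict its conclusion. If girls are already to be randomised, it is enough to state the unit, method and concealment and to make the analysis match.

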#### Inclusion criteria

Being an adolescent girl from 15 to 21 yearsSingle, overweight or obese adolescent girls with PCOS that their diagnosis of PCOS has been confirmed by a gynecologistWillingness to participate in the study and obtaining informed consent from the adolescent and her parents (in cases of younger than 18 years old)Not having a history of diagnosed major mental problems undergoing drug treatmentsNot having any chronic diseases (cardiovascular diseases, diabetes, renal diseases, etc.), which requires special diet prescribed by a physicianNot attending a clinical trial simultaneously

#### Exclusion criteria

Unwillingness to continue cooperation during the trialUse of certain dietary patterns during studyFailure to receive 50% of the intervention for any reason

#### Research variables

In this clinical trial, the designed interventions are considered to be independent variables and.

knowledge, attitude, subjective norms, perceived behavioral control, behavioral intention, and eating practice (behavior) in adolescent girls with PCOS are considered to be dependent variables.

#### Data collection methods

Researcher-made questionnaires evaluating knowledge, attitude, subjective norms, perceived behavioral control, behavioral intention and eating practice (behavior) in adolescent girls with PCOS are used in the quantitative phase of this trial. Reliability and validity of these questionnaires will be determined. Knowledge questionnaire includes 11 questions with three options of “true, false and I do not know”. In measuring knowledge score, one score will be given to the participants for each true answer. Minimum and maximum knowledge scores are 0 and 11, respectively. Attitude questionnaire includes nine questions with a five-point Likert scale of “strongly disagree, disagree, neither agree nor disagree, agree, and strongly agree”. Scoring is done from one to five. Minimum and maximum attitude scores are nine and 45, respectively. Subjective norms questionnaire includes six questions with five options of “never true, rarely true, sometimes but infrequently true, and always true”. In measuring subjective norms score, one score will be given to the participants for each true answer. Minimum and maximum subjective norms scores are six and 30, respectively. Perceived behavioral control questionnaire includes seven questions with a five-point Likert scale of “strongly disagree, disagree, neither agree nor disagree, agree, and strongly agree”. Scoring is done from one to five. Minimum and maximum perceived behavioral control scores are seven and 35, respectively. Behavioral intention questionnaire includes eight questions with five options of “certainly, I do this; most likely, I do this; it is possible, I do this; Unlikely, I do this; and never I do this”. In measuring behavioral intention score, one score will be given to the participants for each true answer. Minimum and maximum behavioral intention scores are eight and 40, respectively. Food frequency questionnaire (FFQ) is used for evaluation eating practice (behavior). Participants were asked to indicate, on average, the frequency of each food item (out of 22) they consumed during the previous one week. The frequency was asked in four categories ranging from ‘never’ to ‘daily’.

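### The scoring sentence for subjective norms and behavioural intention contradicts the stated score ranges of both scales; only 1-to-5 item scoring reproduces those ranges

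*Protocol article*

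**What the plan says.** The Research variables section names six outcomes: "knowledge, attitude, subjective norms, perceived behavioral control, behavioral intention, and eating practice (behavior) in adolescent girls with PCOS are considered to be dependent variables". The next section, Data collection methods, describes a questionnaire for each and, for five of them, gives a minimum and maximum score.

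For subjective norms, the text reads "Subjective norms questionnaire includes six questions with five options of “never true, rarely true, sometimes but infrequently true, and always true". The scoring rule is "In measuring subjective norms score, one score will be given to the participants for each true answer", and the range is given as "Minimum and maximum subjective norms scores are six and 30, respectively".

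For behavioural intention, the text reads "Behavioral intention questionnaire includes eight questions with five options of", followed by five labels running from certain to never. The rule is "In measuring behavioral intention score, one score will be given to the participants for each true answer", and the range is "Minimum and maximum behavioral intention scores are eight and 40, respectively".

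The same section says that attitude and perceived behavioural control are scored from one to five per item, on labels listed from strong disagreement to strong agreement. Knowledge gets one point per true answer, on 11 items.

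**The concern.** For these two scales the item count, the scoring rule and the stated range cannot all hold. A rule that gives at most one point per item cannot produce a total of 30 from six items or 40 from eight.

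The response options do not fit the rule either. The subjective norms labels grade how often something is true, so which of them counts as a true answer is undefined. The intention labels grade likelihood and do not mention truth, so the rule has nothing to count.

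An analyst who followed the sentence literally would analyse a different variable from the one the range describes, or for intention no defined variable at all. Under the Data analysis section the collected data are summarised by mean, standard deviation, minimum and maximum and tested with the listed methods, so the definition of each score carries through to the results.

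**Working it through.** **Inputs**, all from Data collection methods: the number of items n, the item scoring rule and the stated range for each scale.

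**Formula.** If each item scores from a (lowest) to b (highest), the total runs from n × a to n × b.

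**Scales whose stated range agrees with their own rule**
- Knowledge, one point per item: 11 × 0 = 0 to 11 × 1 = 11. Stated 0 to 11.
- Attitude, 1 to 5: 9 × 1 = 9 to 9 × 5 = 45. Stated 9 to 45.
- Perceived behavioural control, 1 to 5: 7 × 1 = 7 to 7 × 5 = 35. Stated 7 to 35.

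**The two scales in question**

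| Item scoring | Subjective norms (n = 6), stated 6–30 | Intention (n = 8), stated 8–40 |
|---|---|---|
| 0 or 1 (the written rule) | 0–6 | 0–8 |
| 0 to 3 | 0–18 | 0–24 |
| 0 to 4 | 0–24 | 0–32 |
| 1 to 4 | 6–24 | 8–32 |
| 1 to 5 | **6–30** | **8–40** |

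The written rule and the stated range share one value on each scale: 6 for subjective norms and 8 for intention. In both cases that value is the maximum under the rule and the minimum of the range.

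Solving backwards gives the same answer. For subjective norms, a = 6/6 = 1 and b = 30/6 = 5. For intention, a = 8/8 = 1 and b = 40/8 = 5. If all items of a scale are scored alike, 1 to 5 is the only item range that fits.

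**Labels.** Subjective norms lists four: never, rarely, then "sometimes but infrequently true, and always true". Scoring from 1 to 5 needs five, which is also the number the text announces.

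**Direction of the intention score.** Reversing an item turns a score x into 6 − x, so a total T on eight items becomes 8 × 6 − T = 48 − T. The limits become 48 − 40 = 8 and 48 − 8 = 40. The range is 8 to 40 either way, so it cannot show which end is high. The intention labels are listed from strongest to weakest, the opposite of the order used for attitude and perceived behavioural control. Numbering them 1 to 5 in the printed order would make a higher total mean weaker intention and would reverse the sign of a group difference.

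**The case against.** The strongest reply is that the intent is plain. Both scales are said to have five options, both ranges equal the item count times 1 and times 5, and two neighbouring scales follow the same pattern with the 1-to-5 rule spelled out. The stray sentence looks carried over from the knowledge scale. No bias between groups is shown, because any consistent scoring applies to both arms. Eating practice, the outcome closest to the trial's aim, is measured by a food frequency questionnaire and is untouched, and the sample size does not depend on this sentence. Most of this stands, and it limits how far the point goes.

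Four stronger readings are tempting, and the document does not support them:
- **The two outcomes cannot be scored at all.** The ranges allow 1-to-5 item scoring to be inferred.
- **The scoring rule could be chosen after seeing the data.** A count is undefined for intention and would openly contradict the published range for subjective norms. Nothing suggests that a count is planned.
- **The knowledge score is faulty too.** A true answer there reads naturally as a correct answer, and 11 items at one point each give exactly 0 to 11.
- **Subjective norms really has four options and a maximum of 24.** The stated five options and the maximum of 30 agree with each other, so a dropped label is the simpler explanation.

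A journal article may also leave full questionnaires and scoring keys to the full protocol. That excuses missing detail. It does not excuse a stated rule that conflicts with the stated range. Nor does the inference of intent supply the fifth label or the direction of the intention score. The questionnaires are made by the researchers, and the article cites no published scoring manual that would settle either.

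**Conclusion.** The point holds. For two of the six outcomes the written scoring rule is wrong against the article's own figures: 0–6 against 6–30 for subjective norms, and 0–8 against 8–40 for intention. Two lesser gaps go with it: one response label is missing for subjective norms, and the direction of the intention score is not stated. The direction is the more consequential of the two, because it decides the sign of a result and the range cannot settle it.

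The inference of 1-to-5 scoring assumes that every item of a scale is scored alike and that the stated item counts and ranges are right. On that footing this is a correctable error in the scoring text. It is not evidence that the instruments are unusable or that a comparison between groups is biased.

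**What to change.** In Data collection methods, replace the true-answer sentence for both scales with: each item is scored 1 to 5, higher meaning more favourable (for intention, never = 1 up to certainly = 5), and the items are summed, giving 6–30 for subjective norms and 8–40 for intention. Supply the missing fifth subjective norms label from the questionnaire itself.

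Make the change before any questionnaire is scored. It costs a few lines of text and needs no extra data, participants or analyses. The knowledge scale needs no change on this account.
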